### Measures

#### Baseline measures

Basic demographic data on age, gender, and ethnicity will be extracted from clinic records and checked with the patients to make sure they are correct.

All patients consenting to take part will be asked to complete a computer-assisted self-completion interview [25,26].

Alcohol consumption will be assessed using the Modified-Single Alcohol Screening Question (M-SASQ). The M-SASQ is a brief validated measure of harmful alcohol use that is acceptable to patients in general medical settings [24]. It consists of a single question - for men: ‘How often do you drink more than eight units of alcohol on one occasion?’ and for women: ‘How often do you drink more than six units of alcohol on one occasion?’ To help people answer this question they are shown a card which describes what a unit of alcohol is. Those drinking at such levels once a month or more are considered eligible. The question on alcohol is embedded in a series of four other questions asking about diet, exercise and smoking.

In addition, eligible patients will be prompted to answer questions on their sexual behavior and health-related quality of life (EuroQol 5 Dimensions (EQ-5D) [27]).

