### Sample size

Initial sample size calculations were based on comparison of the primary outcome. In order to achieve 80% power to detect a mean weekly difference of 23.4 units of alcohol consumption with standard deviation of 58 units [15], 97 evaluable participants per arm were needed. An inflation factor of 1.15 for clustering by clinician in the intervention arm was considered [32], based on an intracluster correlation coefficient of 0.04 [33] and a cluster size of 7 in the intervention arm. Together with an anticipated 30 % drop-out rate at six months, the initial recruitment target was, therefore, 160 per arm.The first months of the trial showed that recruitment and retention rates were higher than expected; the sample size was, therefore, modified to provide additional power to test both the primary and main secondary hypotheses (a reduction in unprotected sexual intercourse) of interest.

The final sample size was based on a practical size of 380 per arm (760 in total). If 65% of participants had unprotected sex in the control group compared to 50% in the intervention arm, the power to detect such an effect would be above 90%, assuming a 25% drop out, and a clustering design effect of 1.15. The power would remain above 80% if the absolute difference is 13%.

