### Statistical analysis

Baseline characteristics will be reported by treatment arm. The primary outcome will be analyzed using random-effects linear regression adjusted for age, sex and harmful alcohol use measured at baseline, testing for the presence of an intervention effect between the two arms. The random-effects model will take into account clustering by sexual health clinic and, in the intervention arm, by treating clinician [34].

Alcohol consumption is not expected to be normally distributed and particular care will be taken to check the validity of the regression, including normality and homoscedasticity of the residuals. If the assumptions are violated, sensitivity analysis will be performed as appropriate.

Participants who dropped out from the trial will be compared to the completers. Sensitivity of the results to missing data will be assessed by performing multiple imputations; further models allowing for missing not at random mechanism will also be considered [35].

The main secondary outcome will be compared in the same way as the primary, using logistic regression and adjusting for unprotected sex at baseline. Other secondary outcomes will be compared using linear or logistic regression, and adjusted for baseline value, as appropriate.

In order to assess for possible heterogeneity of the intervention effect, primary and main secondary outcomes will also be reported by the following subgroups: gender, age (<25, 25 to 35, 35 and older), ethnicity (white vs. other), sexual orientation (heterosexual vs. other). All analyses will be performed according to the randomization arm (intention-to-treat), and two-sided *P*-values considered significant when below 0.05.

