The economic evaluation will take the NHS/Personal Social Services perspective preferred by the National Institute for Health and Clinical Excellence [36] and shown to be the key cost sectors in our previous research of brief intervention for alcohol misuse [30]. Data on uptake of the brief intervention will be collected from records to avoid patients revealing their treatment group to the research assessors. Data on indirect time, including preparation and supervision, will be collected directly from the treating clinician. Data on the use of other health and social services will be collected using the Adult Service Use Schedule (AD-SUS) adapted for alcohol misuse in previous research [30]. The cost of the brief intervention will be directly calculated from salaries using a micro-costing approach [37]. National UK unit costs will be applied to medication, hospital contacts and community health and social services [38,39].

Differences in mean costs will be analyzed using standard parametric t-tests with the validity of results confirmed using bias-corrected, nonparametric bootstrapping (repeat re-sampling) [40]. Despite the skewed nature of cost data, this approach is recommended to enable inferences to be made about the arithmetic mean [41]. Cost-effectiveness will be assessed through the calculation of incremental cost-effectiveness ratios [42] and will be explored in terms of alcohol consumption (primary economic analysis) and quality adjusted life years (QALYs) using the EQ-5D measure of health-related quality of life (secondary economic analysis). Uncertainty around the cost and effectiveness estimates will be represented by cost-effectiveness acceptability curves [43].

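### The cost t-test treats participants as independent although the plan accepts clinician clustering in the intervention arm, so standard errors for the cost difference may be modestly too small

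*Protocol article*

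**What the plan says.** All references are to the protocol article.

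- **Costs (Statistical analysis, economic paragraphs).** "Differences in mean costs will be analyzed using standard parametric t-tests with the validity of results confirmed using bias-corrected, nonparametric bootstrapping". The only justification offered concerns skewness and inference about the arithmetic mean. Independence of participants is not discussed. For the cost-effectiveness results, "Uncertainty around the cost and effectiveness estimates will be represented by cost-effectiveness acceptability curves". The section does not state what unit the bootstrap resamples, or how the cost-effect pairs behind the curves are produced.
- **Clinical outcomes (Statistical analysis).** The primary outcome is analysed by "random-effects linear regression adjusted for age, sex and harmful alcohol use measured at baseline", and "The random-effects model will take into account clustering by sexual health clinic and, in the intervention arm, by treating clinician". The main secondary outcome is handled in the same way, by logistic regression.
- **Sample size.** "An inflation factor of 1.15 for clustering by clinician in the intervention arm was considered", "based on an intracluster correlation coefficient of 0.04 [33] and a cluster size of 7 in the intervention arm".
- **Quality of life (Baseline measures).** "eligible patients will be prompted to answer questions on their sexual behavior and health-related quality of life". EQ-5D is collected again at follow-up.

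**The concern.** The article takes a position on dependence: participants treated by the same clinician in the intervention arm are correlated, by enough to change the sample size and the clinical model. It then names a cost test that assumes no such correlation.

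Clustering of costs is plausible here. Under Planned interventions, the treating clinician delivers the advice and offers the Alcohol Health Worker appointment. The economic paragraphs cost the uptake of the intervention and collect indirect time from the clinician. The Discussion names fidelity across more than 30 clinicians as a challenge. Some of the variation in intervention-arm cost therefore lies between clinicians.

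At stake is the stated precision of the cost difference, which feeds the third hypothesis (cost-effectiveness). The bootstrap is presented as confirming the t-test. If it resamples individuals, it addresses skewness but keeps the same independence assumption, so agreement between the two would not be evidence that the standard error is right.

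**Working it through.** **Inputs from the article.** Difference 23.4 units, SD 58, 80% power, two-sided 5%; design effect 1.15; ICC 0.04 and cluster size m = 7, intervention arm only; 30% drop-out in the initial calculation; final size 380 per arm with 25% drop-out; more than 30 clinicians.

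**Assumptions.** The cost ICC is not given and is varied from 0 to 0.10. A caseload coefficient of variation (CV) of 0.8 is used only to illustrate uneven caseloads; it is not in the documents.

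**Step 1: reproduce the plan's figures.**
- n per arm = 2 × 58² × (1.960 + 0.842)² / 23.4² = 96.4, rounded up to 97, as stated.
- 97 × 1.15 / 0.70 = 159.4, rounded up to 160, as stated.

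The factor 1.15 is thus applied to both arms, as an inflation of the variance of the treatment difference. ICC 0.04 with m = 7 gives 1 + 6 × 0.04 = 1.24 in the intervention arm and (1 + 1.24)/2 = 1.12 averaged over the arms. Neither is exactly 1.15, but 1.12 is close, and the gap does not matter for this point.

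**Step 2: effect of ignoring the plan's own design effect (DE).**
- True SE / naive SE = √1.15 = 1.072.
- SE understated by 1 − 1/1.072 = 6.7%.
- Actual type I error of a nominal 5% test = 2[1 − Φ(1.96/1.072)] = 6.8%, so a 95% interval covers about 93.2%.

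**Step 3: range over the unknown cost ICC.** With clustering in one arm only and equal variances, average DE = [1 + 1 + (m − 1) × ICC]/2. Evaluable participants are 380 × 0.75 = 285 per arm. With 30 clinicians, m = 285/30 = 9.5.

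| Cost ICC (assumed) | m | Average DE | SE ratio | Type I error |
|---|---|---|---|---|
| 0 | either | 1.000 | 1.000 | 5.0% |
| 0.01 | 7 | 1.030 | 1.015 | 5.4% |
| 0.01 | 9.5 | 1.043 | 1.021 | 5.5% |
| 0.04 | 7 | 1.120 | 1.058 | 6.4% |
| 0.04 | 9.5 | 1.170 | 1.082 | 7.0% |
| 0.10 | 7 | 1.300 | 1.140 | 8.6% |
| 0.10 | 9.5 | 1.425 | 1.194 | 10.1% |

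As a check, t-tests were simulated on partially nested normal data (285 per arm, 20,000 runs, participants assigned to clinicians at random). At ICC 0.04 the type I error was 6.3% with 41 clinicians (m about 7) and 7.4% with 30. At ICC 0.10 it was 9.2% and 10.7%.

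**Step 4: uneven caseloads.** Replace m by m(1 + CV²). With m = 9.5 and CV = 0.8 this is 9.5 × 1.64 = 15.58.
- ICC 0.04: average DE = (2 + 14.58 × 0.04)/2 = 1.292, type I error 8.5%.
- ICC 0.10: average DE = (2 + 14.58 × 0.10)/2 = 1.729, type I error 13.6%.

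**Step 5: acceptability curves, conditionally.** Suppose the curves came from resampling individuals and the whole net-benefit variance should be inflated by 1.15. A plotted probability of 0.95 would become Φ(1.645/1.072) = 0.94, and 0.90 would become Φ(1.282/1.072) = 0.88.

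**The case against.** **The cost ICC may be small.** Total cost also includes medication, hospital contacts and community services over six months. The clinician-dependent part is brief advice, a leaflet, an appointment offer, a session of up to 30 minutes and indirect time. If other service use dominates the variance, the cost ICC could lie below 0.04. This stands: the documents do not show that costs cluster as strongly as the clinical outcomes, so the effect is conditional.

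**The size is modest, and a cost p-value is not the main result.** Both parts stand. At the plan's own design effect the type I error is 6.8%, and hypothesis iii is assessed through cost-effectiveness ratios and acceptability curves.

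**A fuller economic plan may supply the detail.** This is right for the resampling unit and the curves, on which the article is silent. It does not rescue the t-test, which the article names and which would have to be replaced.

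Three stronger readings are tempting and are not supported:

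- *That the lack of baseline adjustment also makes results look too certain.* In a randomized comparison the unadjusted difference is unbiased and usually has the larger standard error. For a covariate correlated 0.3 with cost (assumed), the unadjusted SE is 1/√(1 − 0.09) = 1.048 times the adjusted one. What is lost is precision and correction of chance imbalance. Because randomization was stratified by clinic, ignoring clinic also tends to be conservative.
- *That the QALY comparison is unadjusted.* The article gives no method for estimating the QALY difference. The t-test sentence concerns costs only, and other secondary outcomes are "Other secondary outcomes will be compared using linear or logistic regression, and adjusted for baseline value, as appropriate" in the same section. Silence here is not an error.
- *That the acceptability curves will be too narrow.* How they are generated is not stated, so the most one can say is that they may be.

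**Conclusion.** The point holds in a limited form. The named cost test ignores a source of dependence that the article recognises in its sample size and clinical models, and the reason given for the test does not address it. If costs cluster by clinician, the standard error of the cost difference is too small: by about 7% at the design effect of 1.15, with type I error of about 6.8%. Over an assumed cost ICC of 0 to 0.10 with equal caseloads, type I error runs from 5% to about 10%. Higher values need uneven caseloads, for which the documents give no figure. The conclusion rests on a cost ICC above zero, which is plausible from how the intervention is delivered but is not quantified. It is a worthwhile correction because it is cheap and aligns the cost analysis with the clinical analysis, not because the expected error is large.

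**What to change.** 1. Replace the t-test with a linear regression of cost on arm that allows for treating clinician in the intervention arm and for clinic, as the clinical model does. The arm coefficient is still a difference in arithmetic means, so the article's reason for choosing the t-test is kept.
2. State the resampling unit of the confirming bootstrap: clinicians within clinic in the intervention arm, individuals in the control arm.
3. Draw the acceptability curves from the same joint cost-effect replicates.
4. Optionally, and for precision rather than to correct overcertainty, adjust the QALY comparison for the baseline EQ-5D already collected. Baseline service use is not listed among the baseline measures, so baseline cost is not available as a covariate.

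The cost is a change of wording, modest programming and possibly slightly wider intervals. Clinician identity is already needed for the primary analysis, so no new data are required.

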### Ethical issues

Approval for the study was obtained from West London Research Ethics Committee 3 (10/H0706/29) and The Research and Development departments of Chelsea and Westminster Hospital NHS Foundation Trust and Imperial College Healthcare NHS Trust prior to the start of data collection at each local clinic. Only those who agree to provide written informed consent will be included in the study. Each potential participant will be provided with a copy of an information sheet that includes a contact number for the study team.

## Discussion

The SHEAR study is the first large-scale randomized trial to examine the clinical and cost-effectiveness of brief intervention for alcohol misuse for people attending sexual health clinics. We are testing a very brief approach to screening and intervention that is aimed at accurately identifying people who are drinking excessively and helping them reduce their drinking while minimizing any disruption to normal clinical practice. The use of a short (single-item) screening question may have other benefits. It has been argued that previous trials of brief intervention for excessive alcohol use may underestimate the impact of ‘active’ treatment because the process of assessing alcohol use may itself highlight this issue and prompt people to reflect on and consider reducing the amount they drink [44]. In the SHEAR study all material used to publicize and recruit participants refers to alcohol in the context of other lifestyle factors that affect health, such as smoking and diet. We believe that this approach better represents the absence of enquiry or information about alcohol that people currently receive in this and other medical settings, thus allowing us to examine the full impact associated with the brief intervention we are testing.

The form of Brief Advice and referral that we are using is offered to participants after their main health concerns have already been met [45] and includes a brief statement about health consequences of alcohol use, an approach which has been demonstrated to increase uptake of brief alcohol interventions [46]. While this form of intervention has been shown to be acceptable to patients in other settings, we know very little about acceptability in sexual health clinics. We will use quantitative data on levels of uptake of interventions and qualitative data from in-depth interviews with service users and providers to examine the acceptability of screening and Brief Advice to people who are found to be drinking excessively in this setting.

In addition to being large enough to demonstrate reductions in alcohol consumption of a magnitude seen in previous trials, the relatively large sample size means that we have sufficient power to examine clinically important changes in sexual behavior associated with this intervention. While reducing the level of alcohol misuse is worthwhile, the widespread uptake of brief intervention across sexual health clinics may require evidence that any change in drinking are associated with changes in sexual behavior [18]. However, we are only collecting data from people attending three sexual health clinics in London. The findings might not be generalizable to those in rural areas or people with different cultural and socioeconomic backgrounds.

The study faces a number of important challenges, including the need to ensure the fidelity of a brief intervention delivered by over 30 clinicians working across three different clinics, and the need to achieve a high follow-up rate in a relatively young and mobile study population. If we are able to meet these challenges, we will generate data about the clinical- and cost-effectiveness of a form of brief screening and intervention that has the potential to be delivered more widely across sexual health clinics and help establish whether the previously reported association between high alcohol consumption and poor sexual health is a causal one.

### Trial status

Recruitment is on-going (800 participants recruited as of end of April 2012).

## Abbreviations

AD-SUS: Adult Service Use Schedule; AHW: Alcohol Health Worker; AUDIT-C: Alcohol Use Disorders Identification Test-Consumption; EQ-5D: EuroQol 5 Dimensions; M-SASQ: Modified-Single Alcohol Screening Question.
